### **8.3 Data Safety Monitoring (DSM)**

**8.3.1 Quality assurance plan:** The research team plans to devise a Standard Operating Procedures (SOP) in manual form to minimize errors and data loss for both pen-and-paper and computerized tasks. The SOP manual will also minimize the risks of misassignment and prevent breaches of subject confidentiality. Collected data will be backed up and maintained daily. This will prevent data loss, enhances communication between staff, and ensures full data retrieval for analyses. Security will be maintained by the database and statistical core within [name] (DART), which is maintained by the Department of Psychiatry's Information Systems (Psych IS) unit. Personal health information with a code to the subject's identity will be kept on a password-protected computer behind a firewall. Only investigators for this study will have access to the data. The name with a link to the code will be kept in a locked file drawer with limited access. When data are shared with an outside regulatory body or sponsor, such as during reports, activity log, etc., no identifiers will be used, but the data will only contain a study number and clinical information collected during the study.

Internal monitoring of data entry will be conducted by (a) computer programs run on the database to detect values outside the psychometric parameters of the rating scales; (b) direct inspection and rechecking of all safety data by the study coordinator; (c) scheduled monitoring days by all staff, and (d) regular recalibration sessions and recertification of staff. Written reports are generated for these checks, and a tracking system is implemented to prevent systematic errors. Similar procedures are currently being utilized in ongoing studies and meet standards of Good Clinical Practice as set out by the FDA.

**8.3.2 Responsibility for data and safety monitoring:** The Data Safety Monitoring Board (DSMB) has an important role in the oversight of participants' safety. The main role of the DSMB will be to:

1. Review the research protocol and plans for data and safety monitoring.
2. Evaluate the progress of the interventional trial, including periodic assessments of data quality and timeliness, participant recruitment, accrual and retention, participant risk versus benefit, performance of trial sites, and other factors that can affect study outcome. Monitoring also should consider factors external to the study when interpreting the data, such as scientific or therapeutic developments that may have an impact on the safety of the participants or the ethics of the study.
3. Make recommendations to the IRB and investigators concerning continuation or conclusion of the trial.
4. Protect the confidentiality of the trial data and the results of monitoring.

**8.3.3 Data Safety Monitoring Board (DSMB):** A DSMB comprised of three independent faculty members from the Department of Psychiatry will be used for this clinical trial. The DSMB is composed of experts who have conducted randomized controlled trials, two of whom have expertise in substance use disorders. The PI will submit a progress report to the DSMB on an annual basis, which will include a reporting of any adverse events, as well as an update on enrollment, raw data reporting, and outcomes and preliminary analysis if available. Within two weeks of receipt of this progress report, the DSMB will meet (or will stage a teleconference meeting) to review the study's progress. The PI will be present during the first part of the meeting, participating only to provide a verbal update of the study's progress, as well as to answer any questions that the DSMB committee members may have. Following this, the PI will be excused (or she will be asked to leave the teleconference), and the DSMB will conduct a closed-door, private meeting to discuss any pertinent issues. All raw data submitted will be stripped of any identifying information, maintaining participants' confidentiality. The DSMB members will be responsible for monitoring the integrity of the research data and safety environment in accordance with established parameters. The DSMB should monitor the data to assess compliance with the protocol including adherence to protocol participation rules for safety. The DSMB also should monitor the quality and completeness of the data being collected, the frequency of missing or erroneous data, and the presence and frequency of outliers. The monitoring of safety data should include review of adverse events (Aes), serious adverse events

(SAEs), and data reflecting general safety such as clinical laboratory data, treatment retention, and reason for dropout when appropriate. Other parameters are as follows: 1) the quality of the consent process will be monitored — this includes ensuring that changes in the consent process are appropriately addressed with the subject and 2) the maintenance of subject confidentiality will be monitored continuously through the protection of verbal and written subject information. Measures put in place for the protection of subjects' confidentiality will be assessed. The DSMB has the right to make independent representation to the regulatory bodies (HRPO) if there has been a failure in reporting by the principal investigator. The DSMB also has the capacity to instruct the principal investigator to pause or terminate pursuance of research if there is a breach in regulatory guidelines or good clinical practices. The DSMB may provide regular independent reports to the HRPO concerning the protection of human subjects in this study. DSMB review meetings will occur on an annual basis.

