**5.4 Recruitment and informed consent.** New patients will be recruited on the first day of treatment in the clinic (Day 0). At the end of their initial intake procedures of their first day, patients will be asked if they are interested in hearing information about a study that is testing a novel approach to enhancing methadone treatment, for which they would receive paid compensation. The PI will contact the intake coordinator by 9:00 AM to receive a list of patients who are new intakes to the clinic and who are willing to hear about the study. Those patients who indicate their interest will be approached by the PI (or the study research assistant) later that morning as they are awaiting their methadone dosing in the waiting area of the clinic (normal waiting times vary from between 30 minutes to an hour, providing ample time for a consent and scripted recruitment). At this point, the PI will introduce herself, and will assess interest in study participation. Interested patients will be directed to a small interview room located proximal to the waiting area, and a few steps from the nurses' station. The door will be closed, and the investigator will determine whether the patient meets study eligibility criteria (I/E confirmation), and if so, will obtain informed consent and an authorization for release of Health Insurance Portability and Accountability Act (HIPAA) information for specific data related to OUD treatment. The investigator will then assess comprehension with an Evaluation to Sign Consent form (IC Evaluation). Participants will be asked to provide a suitable method of contact (phone number, e-mail, or consent to be contacted through a flag placed on the person's name in Methasoft, the electronic health record platform used at the UMATC). At the end of the baseline meeting, participants will be given an appointment reminder card with follow-up meeting dates for the 4 return visits. On the day prior to each of these meeting dates, contact will be made with the participant to remind him/her of the next scheduled appointment with the study team.

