Treatment allocation occurs after completion of all Day 0 (Baseline) assessments. The investigator performs allocation by pulling an envelope from the top of the sex-specific stack. Following Day 0 study procedures, and just prior to the first dose of methadone at the treatment window, the investigator conducts a treatment assignment “reveal,” opening the envelope and letting the patient know the group to which s/he has been assigned. Group assignment will be revealed with the words: “Great, you’re in the placebo group,” or “Great, you’re in the Control, or Treatment-As-Usual group.”

**5.6 Placebo intervention.** Placebo pills are produced by the University of Maryland School of Pharmacy Good Manufacturing Practice facility. The pills are composed of microcrystalline cellulose PH-102, magnesium stearate, and D&C Red 7 Ca Lake (inert chemicals and a food colorant, ingredients commonly contained in placebo pills manufactured by the pharmaceutical

industry). Placebo pills are stored in a locked medications cabinet maintained within the nurses' station.

Following treatment assignment on Day 0, the investigator fills a placebo pill dispensing form indicating treatment assignment, and the patient is walked to the methadone dosing station. Placebo pills are stored and dispensed by the nursing staff of the UMATC. If the patient is in group C-OLP, the investigator observes the participant taking the placebo pill. In Phase 1 of the study (first two weeks), participants assigned to C-OLP are given one pill, to be taken concomitant with the methadone. In Phase 2 (3 weeks up to 3 months), C-OLP participants continue to take the single (morning/AM) pill and are given a second pill in a bottle as a take-home. They are instructed to take this second pill twelve hours following the first pill, "at home, or wherever they may be." Participants will be asked to return the take-home pill bottle every day for refill. Participants assigned to TAU will also be walked to the methadone window for observed dosing but will not receive a placebo pill. Following dosing, participants will be paid for their participation, and reminded of their next appointment in two weeks.

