**5.7 Post-baseline meetings with study team.** Following the initial (baseline, Day 0) meeting, all participants will be asked to meet with a member of the study team at the following intervals: 14-, 28-, 56-, and 84-days following intake, periods of time that roughly correspond to 2 weeks, 1-, 2- and 3-months of treatment. Participants will be paid \$25 for each 30- to 45-minute study visit, for a total possible \$125. Because study participants are clients of the UMATC, they must come to the clinic daily for the first several months of their OUD treatment, facilitating follow-up with the study team (the research study team is co-located at the UMATC).

**5.8 Blinding.** At all stages of the study, methadone dose adjustments are conducted by an independent clinician blinded to treatment allocation and to when a participant is enrolled in the study. Additionally, because treatment allocation occurs only after Day 0 (baseline) assessments are complete, study team members are blind to treatment assignment for all of Day 0 procedures. Finally, data analysts are blind to treatment allocation.

**5.9 Urine toxicology screens.** Urine drug screening will occur *via* two methods: (1) a point-of-care Quik-tox screen (11 panel; LabCorp) conducted by clinic staff, results of which are reported immediately, conducted at baseline and then at monthly (random) intervals post-baseline; (2) and liquid chromatography–tandem mass spectrometry (LC-MS/MS) testing for a panel of more than 240 drugs, including new psychoactive substances, as well as other illicit and prescription

drugs. All testing is conducted by the Division of Forensic Toxicology, Armed Forces Medical Examiner System and coordinated by the University of Maryland, College Park Center for Substance Abuse Research (CESAR) staff. Urine is collected from participants during each of the five meeting times, and the Quik-tox screen is conducted only on samples from meeting one (baseline); the LC/MS/MS testing is conducted on all samples (baseline and 2 weeks, and 1-, 2- and 3-months post-baseline screening).

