copy of the form will be kept on file. Authorized research team members will obtain informed consent and will answer any questions the participant may have. At the end of the consent procedure, they will also ask questions to test the participant's knowledge of the study. Participant understanding will be assessed using the HRPO "Evaluation to Sign Consent Form", available at [https://www.umaryland.edu/media/umb/oaa/hrp/documents/study-tools-docs/eval\\_consent.pdf](https://www.umaryland.edu/media/umb/oaa/hrp/documents/study-tools-docs/eval_consent.pdf). Participants will be consented for the procedures that will take place during the entire study period; as such, the consent form will cover all treatments and procedures that will occur within that period of the participant's involvement in the investigation. Subjects will be reminded, however, at each of the meetings with the PI that participation is entirely voluntary, and that s/he has the right to withdraw at any time. Consent will include clearly communicated information that participation in the study will not affect an individual's status as a patient at this, or any other methadone treatment clinic.

**9.6.2 Protections Against Risk.** All research investigators and staff will maintain current training in human subject protections as IRB mandated, and all will be trained with well-specified policies and procedures regarding participant well-being. Questionnaire items and rating scales will be administered by the P.I. or research assistant after obtaining informed consent. All study team members will receive thorough training on study-specific procedures. Further, our ongoing staff training, supervision, and research procedures include pro-active and sensitive monitoring of participant well-being during research encounters (both research intervention and assessments) and responding appropriately to their needs in a wide range of situations, research protocol adherence, and assessing reporting and responding to all adverse events. At all stages of the study, access to trained psychiatrists and medical personnel with experience dealing with this patient population will be available to respond to any unforeseen crisis and to ensure protections against risk.

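### The PI's annual DSMB report may carry interim outcomes to someone who recruits and assesses later participants

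*Protocol*

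**What the plan says.** **The report.** Protocol 8.3.3: "The PI will submit a progress report to the DSMB on an annual basis". Besides adverse events it contains items listed "as well as an update on enrollment, raw data reporting, and outcomes and preliminary analysis if available". The PI attends the first part of the board's meeting and then leaves before a private session.

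**The board.** Section 8.3.2 asks it to "Protect the confidentiality of the trial data and the results of monitoring" and to "Make recommendations to the IRB and investigators concerning continuation or conclusion of the trial".

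**The PI's other roles.**
- Recruitment (5.4): interested patients "will be approached by the PI (or the study research assistant) later that morning".
- Allocation (5.5): "The investigator performs allocation by pulling an envelope from the top of the sex-specific stack". The same person then reveals the arm. This section says investigator, not PI.
- Assessment (9.6.2): "Questionnaire items and rating scales will be administered by the P.I. or research assistant".

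**Blinding (5.8).** Methadone dose is adjusted throughout by a separate clinician who knows neither the arm nor whether the patient is enrolled. The study team is blind for Day 0 procedures. In addition, "data analysts are blind to treatment allocation".

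**Outcomes.** The primary outcome is dose taken from clinic charts (6.1). The OOWS is scored by the experimenter (6.2.4). The other scales are facilitated self-report, with a team member filling in the answers (6.2, 9.1).

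**The concern.** Interim outcome results are normally kept from people who recruit or assess participants, because knowing which way the results point can colour later work. The closed session appears designed for that purpose. Here, however, outcome material may pass through the PI's hands before the session starts.

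Two outcome types are open to influence: the OOWS, where the rater judges whether each sign is present, and facilitated self-report, where a staff member asks the questions and records the answers. Recruitment is also exposed to some degree. The intervention works through expectancy, and the Appendix 1 script is a conversational guide that tells patients the placebo may or may not work. A recruiter who has seen interim outcomes may find it harder to say that neutrally.

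What is at stake is the credibility of those Aim 2 secondary outcomes for participants recruited or followed after such a report.

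**Working it through.** **1. Does the text put interim results before an unblinded assessor?** Four statements taken together:

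| Question | Protocol | Answer |
|---|---|---|
| Who submits the report? | 8.3.3 | The PI |
| May it contain outcomes and preliminary analysis? | 8.3.3 | Yes, if available |
| Who recruits and rates? | 5.4, 9.6.2 | The PI or a research assistant |
| Is that person blind after Day 0? | 5.8 | Not claimed |

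The route therefore exists on the text. Four of the five meetings (Days 14, 28, 56 and 84) come after the arm is revealed, and the OOWS is scheduled at all of them. Coding the arms in the PI's report would give limited protection, since someone who knows individual assignments could decode the groups.

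**2. How many participants could be affected?** The protocol gives 4 to 8 intakes per week (section 4.0), a target of 120 and follow-up of 84 days = 12 weeks. The enrolling share is not given; I assume 100%, 50% and 25%, steady accrual, no dropout and a first report at week 52.

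- Accrual time = 120 / (intakes per week × share): 15 to 30 weeks at 100%, 30 to 60 at 50%, 60 to 120 at 25%.
- Adding 12 weeks, the last visit falls at week 27 to 42, 42 to 72, or 72 to 132. That allows 0, 0 to 1, or 1 to 2 annual reports.
- Participants with at least one assessment period after week 52, by enrolment rate:
  - 4 or more per week: all complete by week 42, so 0.
  - 2 per week: 120 − 104 = 16 not yet recruited, plus 12 × 2 = 24 in follow-up, so 40.
  - 1 per week: 120 − 52 = 68 not yet recruited, plus 12 × 1 = 12 in follow-up, so 80.

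The range is 0 to 80 of 120. These are counts of people potentially exposed, not estimates of bias.

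**3. Does the type I error change?** The sample size in 7.1 assumes one two-tailed .05 Fisher exact test with 60 per group and 70% against 44% (at most 26/60). Exact enumeration gives power 0.806 at 26/60 and 0.784 at 44.0%, which agrees with the stated .80 for a single analysis.

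If K equally spaced looks were each tested at |Z| > 1.96, and any significant one could end the trial or be claimed, the overall error would be P(max |Z_k| > 1.96), with corr(Z_j, Z_k) = √(t_j / t_k) for j < k:

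- Information 1/2, 1 (one interim): 8.3%
- Information 1/3, 2/3, 1 (two interims): 10.7%

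The protocol states none of those conditions. Section 8.2.3 covers only discontinuing individuals for safety. The board's power to pause or terminate (8.3.3) is tied to breaches of regulatory guidelines or good clinical practice. The review at 50% enrolment (8.0) is for outliers, coding errors and similar problems. If only the final test supports a claim, the error stays at 5.0%.

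**The case against.** The strongest reply is that the text is milder than it first looks. The PI submits the report; nothing says the PI runs the analysis, that results are split by arm, or that outcomes appear every year. Analysts are blind, and a research assistant may do the recruiting and rating. This stands: the exposure is permitted, not certain.

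Second, the underlying weakness is unblinded assessment after Day 0, which rewording 8.3.3 does not cure. Investigators also have access to the study data in any case (8.1, 8.3.1). This stands too. The report adds to an existing risk, and closing this route does not close every route.

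Third, much of the trial is shielded. Dose comes from charts and is adjusted by a blinded clinician. Retention comes from clinic records. The LC-MS/MS urine testing is done by an outside laboratory. The reveal has parallel set wording for both arms, and the script and video come before allocation, so they reach both arms alike. This confines the point to the OOWS and the facilitated self-report.

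Several stronger readings are tempting but not supported:
- **That the annual reports inflate the false-positive rate.** A reader might infer this from the board's power to recommend conclusion. That is general board wording; no interim efficacy test or efficacy stopping rule is stated.
- **That the report contradicts the board's confidentiality duty.** The duty binds the board. An investigator supplying trial data to it does not breach it.
- **That the closed session is pointless.** It still lets the board deliberate without the PI, including on failures of reporting by the PI.
- **That 5.8 blinds only the analysts.** It also blinds the dose-adjusting clinician throughout and the study team on Day 0.

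**Conclusion.** The point holds in a limited form. Section 8.3.3 permits a report through which interim outcomes can reach a person who recruits and assesses later participants while knowing their arm, and the closed session does not prevent that. The outcomes at risk are the OOWS and the facilitated self-report measures; the primary outcome is not exposed through this route.

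The bias cannot be sized from the protocol. The number of participants with assessments still to come after a first annual report could be anywhere from none to about 80 of 120, depending on an enrolment share that the protocol does not give, and it matters only if that report contains outcome results.

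Type I error remains 5% on the text as written. The 8.3% and 10.7% figures describe a trial in which each look is tested at .05 and can end the study or support a claim, which this protocol does not plan. The change is worth making because it is cheap and, with no efficacy stopping planned, the PI has no stated need for interim outcome results.

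**What to change.** In 8.3.3:

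1. Remove outcomes and preliminary analysis from the PI's report. Limit it to enrolment, retention, data quality and adverse events, without comparative outcome results. Retention is itself a secondary outcome, so it should be given pooled over arms.
2. Have the existing data analyst send any by-arm tables directly to the board's closed session. These must include by-arm adverse events, so that the board keeps what it needs to weigh risk against benefit.
3. State that interim outcome data are descriptive only and that no comparative efficacy test is made before database lock.

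The cost is a wording change plus a separate closed-session table from the analyst. The PI gives up sight of interim comparative results. Arms can be coded in the analyst's tables to respect 5.8, although adverse events attributed to the pill can arise in only one arm and may reveal the code. The change does not address unblinded assessment after Day 0 or the investigators' access to the database.

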## **9.0 PROTECTION OF HUMAN SUBJECTS**

**9.1 Behavioral (instrument) data collected.** All behavioral assessment data will be collected with a facilitated self-report (i.e., a member of the study team will administer and fill in participant responses to the assessments) during each of the 5 meetings with participants. All administered assessments are described in an earlier section and in Table 1.

**9.2 Electronic Health Record Data Collected.** Consent will be obtained from each participant allowing for select information to be obtained. These data include: clinic attendance, clinic retention/discharge, and clinic urine drug screen test results at intake and monthly thereafter.

**9.3 Intervention:** Daily Placebo Pill Dispensing for Placebo Arm. Following treatment assignment on Day 0, the investigator will fill a placebo pill dispensing form indicating treatment assignment, and the patient will be walked to the methadone dosing station. Placebo pills will be stored and dispensed by the nursing staff of the UMATC. If the patient is assigned to the Placebo (C-OLP) arm, the investigator will observe the participant taking the placebo pill. In Phase 1 of the study (first two weeks), participants assigned to OLP will be given one pill, to be taken concurrently with the methadone. In Phase 2 (3 weeks up to 3 months), Placebo arm participants will continue to take the single (morning, or AM) pill, and will be given a second pill in a bottle as a take-home. They will be instructed to take this second pill twelve hours following the first pill, "at home, or wherever they may be." Participants will be asked to return the take-home pill bottle every day for refill. Circumstances may occur under which a participant may

need to be withdrawn from the protocol and include not following instructions given by team members.

**9.4 Materials: Placebo Pills.** The placebo (C-OLP) pill is produced by the University of Maryland School of Pharmacy Good Manufacturing Practice facility. The pills are composed of microcrystalline cellulose PH-102, magnesium stearate, and D&C Red 7 Ca Lake (inert chemicals and a food colorant, ingredients commonly contained in placebo pills manufactured by the pharmaceutical industry). Placebo pills are stored in a locked (Pxyis MedStation) medications cabinet maintained within the nurses' dosing window area.

**9.5 Risks to Human Subjects.** Risks of participating in research will be clearly communicated to participants in the informed consent form. These include:

- Loss of Confidentiality (highly unlikely, very serious)
- Breach of privacy (highly unlikely, serious)
- Risks associated with psychological questionnaires (highly unlikely, not very serious)
- Risks associated with the time-limited nature of the study (somewhat likely, not serious)
- Unforeseen adverse reactions to the placebo pills (highly unlikely, moderately serious)
- Unknown Risks (highly unlikely, moderately serious)

